#### Participant recruitment and study procedure

Participants will be recruited from surgical outpatient by trained research assistants. Patients with uncomplicated 3rd- or 4th-degree hemorrhoids will be assessed for study eligibility using a screening log. Written informed consent will be obtained from the eligible participants.

The patients admitted for elective hemorrhoidectomy will undergo pre-anesthetic evaluation the day before surgery and will be given fasting guidelines including 6 h for solid foods and 2 h to anesthesia for clear fluids like water. All patients will receive prophylactic antibiotics (intravenous 500 mg of metronidazole) within 60 min prior to incision [18]. Two hours before surgery, the patient will be receiving an enema intrarectal. All patients scheduled for surgery will be informed and admitted a day prior to surgery, prepared, and included in the theater program in order to maintain continuity of care.

Once in the operating room, vital signs will be taken (blood pressure, pulse rate, oxygen saturation, and monitoring of the ECG). Co-loading of intravenous crystalloids, namely normal saline and or ringers’ lactate, will be done using a restrictive approach of fluid administration and undergo open hemorrhoidectomy under saddle block [19].

Aseptic protocols will be observed for all groups. Group A patients, in lithotomy or prone jack-knife positions, will be infiltrated with bupivacaine 0.5% at a maximum safe dose of 2 mg/kg with adrenaline (1:200,000) following the technique of Jinjil et al. [20]. The local anesthetic mixture will be administered by the principal investigator as follows: The first two injections will be applied bilaterally (1 and 4), 5 mm from the border of the perianal skin, and the mixture will be injected at 12 and 6 o’clock (3 ml each side). Thereafter, further 4 injections will be administered into 4 quadrants performing a diamond shape (2, 3, 5, and 6), 5 mm from the anal opening; every 1 ml will be injected at a 4-cm, 3-cm, and 2-cm depth from the skin, respectively, as shown in Fig. 1.

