#### Independent variables

Data will be captured on preoperative independent variables such as gender, age, ASA level, and degrees of the hemorrhoids.

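### Minor: the infiltration volumes are not tied to weight and, on the most natural reading, pass the protocol's own 2 mg/kg bupivacaine maximum below 45 kg; the text does not reconcile the two.

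*Protocol article*

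**What the plan says.** All the relevant text is in the protocol article, section *Participant recruitment and study procedure*, in the paragraph on group A.

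- **Concentration and ceiling.** Patients "will be infiltrated with bupivacaine 0.5% at a maximum safe dose of 2 mg/kg with adrenaline" at 1:200,000. The ceiling therefore scales with body weight.
- **First injections.** "The first two injections will be applied bilaterally (1 and 4), 5 mm from the border of the perianal skin". The same sentence places the mixture at 12 and 6 o'clock and gives 3 ml for each side.
- **Further injections.** "further 4 injections will be administered into 4 quadrants performing a diamond shape (2, 3, 5, and 6"), for which "every 1 ml will be injected at a 4-cm, 3-cm, and 2-cm depth from the skin, respectively".

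The paragraph states no total volume or total dose, no further dilution and no adjustment of the volumes for weight. It does not say what happens when the listed volumes and the ceiling disagree. It refers to a published technique and to Fig. 1 for the injection pattern.

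**The concern.** One paragraph describes the experimental intervention in two ways: a limit that moves with weight, and a set of volumes that does not. Any such pair must cross at some body weight. Below that weight, giving every listed volume breaches the limit, and respecting the limit means that not every listed volume can be given.

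Two things are at stake. The first is patient safety, because the figure exceeded is one that the protocol itself calls a safe maximum. The second is the definition of the intervention. Group B receives one stated spinal volume (1.5 ml of 0.5% bupivacaine). In group A, what a light patient receives depends on how the operator resolves the conflict, and the text does not say which injection or depth would change.

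**Working it through.** The document gives no total to reproduce, so the check is a direct sum from its own figures.

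**Inputs**

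- Concentration: 0.5% = 5 mg/ml (unit conversion). This assumes that the mixture injected is still at 0.5%; the text mentions no dilution.
- Ceiling: 2 mg/kg.
- First injections: 2, at 3 ml each.
- Further injections: 4, with 1 ml at each of 3 depths.

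**Most natural reading**

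- Volume = 2 × 3 ml + 4 × (3 × 1 ml) = 6 + 12 = 18 ml.
- Dose = 18 ml × 5 mg/ml = 90 mg.
- Weight at which dose equals ceiling = 90 mg ÷ 2 mg/kg = 45 kg.

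| Body weight | 90 mg expressed per kg | Ceiling in mg (2 mg/kg × weight) |
|---|---|---|
| 35 kg | 2.57 mg/kg | 70 |
| 40 kg | 2.25 mg/kg | 80 |
| 44 kg | 2.05 mg/kg | 88 |
| 45 kg | 2.00 mg/kg | 90 |
| 50 kg | 1.80 mg/kg | 100 |
| 60 kg | 1.50 mg/kg | 120 |

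At 40 kg the excess is 2.25 ÷ 2 − 1 = 12.5%. From 45 kg upwards there is no conflict on this reading. The weights are illustrations; the document gives no weight distribution.

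**How far the result depends on the reading**

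| Reading | Volume | Dose at 5 mg/ml | Crossing weight |
|---|---|---|---|
| Each of the four later injections is 1 ml in all | 6 + 4 = 10 ml | 50 mg | 25 kg |
| 1 ml at each of three depths, four times | 6 + 12 = 18 ml | 90 mg | 45 kg |
| As above, but 3 ml on both sides at both 12 and 6 o'clock | 12 + 12 = 24 ml | 120 mg | 60 kg |

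The middle reading fits best. The numbering (1 and 4, then 2, 3, 5 and 6) gives six injections in all, which argues against four separate 3 ml deposits at the start. Three depths are listed for 1 ml each, and three depths cannot be matched one to one with four injections, so they are best taken as three deposits within each injection. The wording still leaves room for the other two readings: it calls the first pair bilateral and speaks of each side, yet 12 and 6 o'clock lie in the midline.

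**The case against.** The strongest reply is that a maximum already tells the operator which instruction yields. By its ordinary meaning a ceiling limits whatever is listed beneath it, and the article never says that the volumes are mandatory for every patient. This largely stands, and it is the main reason why the point is minor. What it leaves open is the procedure: the text does not state that the ceiling overrides the volumes, nor how six numbered injections change if it does.

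The second reply is that the 90 mg total is a reading and not a stated figure. This also stands. On the 10 ml reading the crossing weight is 25 kg, and the conflict practically disappears for adults. Fig. 1 and the cited technique are not available here and could settle the volumes or show a dilution. Against this, one sentence that can yield 50, 90 or 120 mg would gain from a stated total in any case.

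A reader might be tempted to go further in four ways that the document does not support.

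- *That group A as a whole is overdosed.* On the most natural reading nobody at or above 45 kg exceeds the ceiling.
- *That the eligibility criteria wrongly lack a weight limit.* The inclusion and exclusion lists contain none, but a per-kg ceiling can do its work without one, so the absence is not an error.
- *That weight and volume go unrecorded.* The *Independent variables* section names "preoperative independent variables such as gender, age, ASA level, and degrees of the hemorrhoids", an open list of examples. A pre-anesthetic evaluation is planned the day before surgery, and an article commonly leaves form fields to the full protocol.
- *That the pain comparison is biased.* Nothing shows that patients light enough to be affected were enrolled, and a dose that varies with weight under a cap is not in itself an undefined intervention.

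**Conclusion.** The point holds in a narrow form. The article gives a 2 mg/kg maximum and weight-independent volumes for the same infiltration and does not reconcile them. On the most natural reading, and if the mixture is undiluted, the volumes come to 90 mg and exceed the maximum below 45 kg. Across the readings that the wording allows, the crossing weight runs from 25 to 60 kg.

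The number of patients affected cannot be found from the document. Among adults aged 18 to 65, with 29 per arm, it is probably small; that is an assumption. Severity is minor: it is an unreconciled instruction with a bearing on safety, and no effect on the trial's comparison has been shown.

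**What to change.** The investigators should reconcile the listed volumes in *Participant recruitment and study procedure* with the protocol's own per-kg maximum. The text should state the total volume that the injection scheme is meant to deliver, confirm whether the mixture is given at 0.5%, and say which instruction governs when the two conflict. If Fig. 1 or the cited technique already answers this, a cross-reference with the total is enough.

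The choice is a clinical one for the investigators; no dose, weight limit or rule is proposed here.

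The cost is about one sentence. Recruitment was planned to end on 31 May 2022, before the article appeared in August 2022. For patients already treated, the same sentence can go into the trial report as a statement of which instruction was followed.

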**Fig. 1 Fig1:**
[figure not shown]
Local anesthesia infiltration [20]

With this technique, the mixture will fill the inter-sphincteric space and block the inferior rectal branch of the pudendal nerve (S2, S3) and the perineal branch of the 4th sacral nerve, causing paralysis of the external sphincter.

For group B patients, the back will be cleaned with 70% alcohol and draped while in a sitting position. The anesthetist or the anesthesiologist will identify the L4/L5 interspace by anatomical landmarks. Lidocaine will be infiltrated in the skin and subcutaneous tissue to form a wheel in the skin. A 25-G quincke spinal needle will be introduced into the sub-arachnoid space using either the midline or paramedian approach as deemed necessary by the anesthetist. Once the free flow of cerebrospinal fluid is observed in the hub of the needle, 1.5 ml of 0.5% bupivacaine will be administered. The patient will be kept in the sitting position for 10 min and thereafter placed in supine. Time 0 will be reordered once the cleaning of the back starts.

After the proof of the effect of anesthesia is administrated, participants in both groups will be put in lithotomy position, and the perianal region will be cleaned and draped before the beginning of open hemorrhoidectomy which will be done by the principal investigator. The technique for open hemorrhoidectomy will be as described by Milligan Morgan Clinic [21] after which dressing will be done, and this will be documented as a time finale.

Analgesia will be given according to the visual analog scale (VAS) once it is rated more than 4 by the patient at 2, 4, and 6 h for all patients irrespective of the type of anesthesia, and all participants will be discharged based on the post-anesthesia discharge scoring system (PADS) for determining home-readiness whereby the patient is judged fit for discharge when his score is ≥ 9 [22] and the 7th day assessment will be done after the patient is called back by the research assistants. Participants will be reassessed using the VAS on the 7th day postoperative. Diclofenac sodium 100 mg oral 8 hourly for 5 days will be considered as rescue analgesia postoperatively. All patients will be receiving a tablet of metronidazole 400 mg 8 hourly for the following five postoperative days.

The follow-up research assistants different from the recruiting team will collect the outcome data from patients at a stipulated time and enter it into a Microsoft Excel sheet up to the 7th day postoperative.

On the 7th day postoperative, the patients will be called back for review and follow-up assessment. Those who will not be able to come back to the hospital after discharge will be interviewed on a telephone call.

During both visits, detailed information will be obtained by the study doctor. The entire process from patient allocation to follow-up is displayed in Fig. 2 and well described in a Standard Protocol Items: Recommendations for Interventional Trials (SPIRIT) figure in Fig. 3.

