**Discussion:**

The primary outcome of this study is to compare the occurrences of postoperative pain following open hemorrhoidectomy using the visual analog scale in an interval of 2, 4, and 6 h and 7 days postoperatively. Furthermore, the mean operative time from the induction of anesthesia to the end of the surgical procedure as well as the cost-effectiveness of the 2 techniques will be assessed in both groups. Open hemorrhoidectomy under local anesthesia has the potential to offer benefits to patients but most importantly expediting return to baseline and functional status, shorter hospital stay by meeting the faster discharge criteria, and reduction in costs associated with reduced length of stay and complications.

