#### Secondary outcome variable

The mean operative time from anesthesia induction to the end of open hemorrhoidectomy will be recorded in both groups.

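### Operative time is defined from anesthesia induction in both groups, but the saddle-block clock starts earlier, at back cleaning, and local anesthesia has no equivalent start

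*Protocol article*

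**What the plan says.** The section on the secondary outcome variable states: "The mean operative time from anesthesia induction to the end of open hemorrhoidectomy will be recorded in both groups". The Discussion part of the abstract gives the same interval: "the mean operative time from the induction of anesthesia to the end of the surgical procedure". Neither place says which event counts as induction.

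The procedure text after Fig. 1, in the paragraph on group B (saddle block), opens with "For group B patients, the back will be cleaned with 70% alcohol and draped while in a sitting position". It then describes finding the interspace, lidocaine infiltration of the skin, placing the spinal needle and the intrathecal injection. After the injection, "The patient will be kept in the sitting position for 10 min and thereafter placed in supine". The paragraph closes with the clock rule: "Time 0 will be reordered once the cleaning of the back starts" (the verb is evidently meant as recorded).

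For group A (local anesthesia), the section on participant recruitment and study procedure goes from positioning to infiltration: "The local anesthetic mixture will be administered by the principal investigator as follows", and then "The first two injections will be applied bilaterally (1 and 4), 5 mm from the border of the perianal skin". It sets no time 0. Preparation before infiltration is covered only by a general sentence: "Aseptic protocols will be observed for all groups".

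The stop is common. It is recorded after dressing and described for both groups together.

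**The concern.** The two start rules disagree for saddle block, and the one rule tied to an observable event cannot be applied to local anesthesia, because that arm has no back cleaning. Followed literally, the text times the arms from different kinds of event: start of preparation in one, induction in the other.

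Operative time is specific objective ii and the only secondary outcome, and means are to be compared by a two-tailed t-test at p<0.05. The introduction uses shorter operative time as part of the case for local anesthesia. A systematic difference in when the clock starts moves the mean difference by its full length, and a larger sample does not remove it.

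The people in theater also know the arm. Blinding covers patients and outcome assessors, while the principal investigator infiltrates the local anesthetic and operates in both arms. An undefined start in group A is therefore left to the judgement of unblinded staff.

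**Working it through.** **Step 1: start and stop by arm, as written.**

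| | Saddle block (B) | Local anesthesia (A) |
|---|---|---|
| General definition (abstract; secondary outcome) | induction | induction |
| Procedure text | start of back cleaning | none given |
| Stop | after dressing | after dressing |

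The common stop does not offset the unequal start.

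**Step 2: what the mismatch does.** Let *b* be the time in arm B from start of back cleaning to the injection taken as induction. Let *a* be the time in arm A from start of its preparation for the anesthetic to the first injection. Let I_B and I_A be the times from injection to end of dressing. Suppose arm A is timed from the first injection.

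- Recorded difference (B − A): b + I_B − I_A
- Difference if both start at preparation: (b + I_B) − (a + I_A)
- Difference if both start at injection: I_B − I_A

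The recorded difference exceeds the preparation-based one by *a* and the injection-based one by *b*. Neither can be negative, so on this supposition the shift favours local anesthesia whichever common start is the reference. Its size depends on that choice. If arm A is instead timed from its own preparation, the recorded difference equals the preparation-based one and the shift disappears.

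**Step 3: what is not artefact.** The 10 min of sitting in arm B follows the intrathecal injection. It lies inside I_B under either start and is not part of the mismatch.

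**Step 4: illustration of size.** The document gives no figure to reproduce here: no duration for *a* or *b*, and no SD for operative time. Both the offset and the SD below are assumptions. From the document come 29 per arm and a two-sided test at 0.05.

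SE = SD × √(2/29), noncentrality = offset/SE, df = 29 + 29 − 2 = 56, critical |t| = 2.003. The result is the probability of p<0.05 from the offset alone, with no true difference.

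| Assumed offset | Assumed SD 5 min (SE 1.313) | Assumed SD 10 min (SE 2.626) | Assumed SD 15 min (SE 3.939) |
|---|---|---|---|
| 1 min | 0.12 (noncentrality 0.76) | 0.07 (0.38) | 0.06 (0.25) |
| 3 min | 0.61 (2.28) | 0.20 (1.14) | 0.12 (0.76) |

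The nominal level is 0.05. A short offset with a wide SD does little harm; a few minutes with a narrow SD does a good deal.

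**The case against.** The strongest reply is that the direction of bias is inferred. Induction is not defined, and back cleaning could be read as the start of the anesthetic procedure in arm B, with the same reading carried over to arm A's aseptic preparation. On that reading both clocks start at preparation and there is no bias. A condensed article may also leave group A's time stamp to the full protocol or the data form. This stands as far as direction goes: a reader might infer that an advantage for local anesthesia is built into the outcome, and the document does not establish that. It does not remove the contradiction between the stated definition and the group B rule.

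Second, finding the interspace, infiltrating the skin and placing the needle are genuine parts of saddle block, so counting them measures what the technique takes. This also stands. It would be wrong to treat all of arm B's preparation as error: if the intended interval starts at preparation, the error is only arm A's uncounted preparation, which may be short. Larger assumed offsets, such as 5 min with an SD of 5 min, give a probability of 0.96, but nothing in the document supports that as the expected size.

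Third, a scenario of no true difference may be unrealistic, because arm B sits for 10 min after the injection. Arm A's wait for onset is not given, so the net difference is unknown. If a real difference exists, the likelier harm is an overstated mean difference and not a false-positive test. That is fair, and it is a reason to read the probabilities in the working as a scale only.

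Finally, operative time is secondary; pain is the primary outcome. That limits the weight of the point, not its validity.

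**Conclusion.** The point holds as an internal contradiction. The abstract and the secondary-outcome section start operative time at induction in both groups. The procedure text starts it earlier for saddle block, at a step the other arm does not have, and gives local anesthesia no equivalent. This is more than omitted detail, because applying the written rules literally gives the arms different start events for a tested outcome.

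The shift in favour of local anesthesia is conditional on arm A being timed from its first injection, the most natural reading of the only rule that covers it. The amount cannot be derived from the document. On assumed net offsets of 1 and 3 min, with SDs of 10 and 5 min, the chance of a significant result from the offset alone is about 0.07 to 0.12 and 0.20 to 0.61, against 0.05. The correction is worth making because it is cheap; the primary outcome is not affected.

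**What to change.** Reconcile the abstract, the secondary-outcome section and the group B procedure text by naming one equivalent start event in both arms. Either of two would do:

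- **Start of skin preparation for the anesthetic.** In arm B this is back cleaning. In arm A the text must say explicitly that it is the preparation before infiltration. The only perianal cleaning now described comes after the anesthetic has taken effect, in both groups, and starting arm A there would reverse the asymmetry.
- **First anesthetic injection.** In arm B the text should say whether the skin lidocaine or the intrathecal injection is meant.

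Keep the common stop at the end of dressing.

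The cost is a sentence of text and one clearly defined time stamp on the form. The harder part is retrospective: 45 of 58 patients were registered by 7 April 2022, leaving 58 − 45 = 13. For patients already operated on, recover the matching time from theater records where it is available. The document does not show that those records hold it. Where it is not available, the report should disclose how each arm was timed.

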### Study variables

#### Primary outcome variable

The occurrence of pain following open hemorrhoidectomy will be determined in both groups using the area under the curve (AUC) for visual analog scale (VAS). The VAS will be used in an interval of 2, 4, and 6 h and 7 days postoperatively (the lower end of the scale labeled “0” means no pain while the upper end of the scale “10” signifies the worst imaginable pain).

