### Data processing and analysis plan

Data will be statistically analyzed using IBM Statistics SPSS for Windows 23.0. The primary outcome will analyze all randomized patients (on an intent-to-treat (ITT) basis) and per-protocol (PP) population. The mean pain scores at rest and their standard deviations will be computed and compared using one-way ANOVA tests. VAS will be stratified as ordinal (0 as no pain, 1–3 as mild, 4–6 as moderate, and 7–10 as severe); the significance of the difference in the mean scores between local and saddle groups will be determined by the Kruskall-Wallis (*H*) test at 95% confidence interval, regarding *p* < 0.05 as statistically significant; furthermore, the mean pain scores will be analyzed for significant differences in the area under the curve (AUC) for VAS (2-sample *t*-test). The mean operative time and standard deviation will be computed for each technique of open hemorrhoidectomy. Cross tabulation will be performed between the two open hemorrhoidectomy techniques for categorical cost-effective analysis. The difference in the means will be compared using the *t*-test and their corresponding two-tailed p-value, regarding *p* < 0.05 as statistically significant.

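### The VAS scores that form the primary outcome also trigger rescue analgesia, and no outcome captures rescue use, so unequal rescue can hide a pain difference at 4 h and 6 h

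*Protocol article*

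**What the plan says.** **Outcome.** Under Primary outcome variable, pain is measured by the AUC of the VAS: "The VAS will be used in an interval of 2, 4, and 6 h and 7 days postoperatively".

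**Rescue.** Under Participant recruitment and study procedure (text after Fig. 1): "Analgesia will be given according to the visual analog scale (VAS) once it is rated more than 4 by the patient", and this applies "at 2, 4, and 6 h for all patients irrespective of the type of anesthesia". A little further on: "Diclofenac sodium 100 mg oral 8 hourly for 5 days will be considered as rescue analgesia postoperatively". The article does not say in so many words that the analgesia given above 4 is this diclofenac course. Reading the two sentences together is the natural interpretation and is used here.

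**Analysis.** Under Data processing and analysis plan: "The mean pain scores at rest and their standard deviations will be computed and compared using one-way ANOVA tests". VAS categories go to a Kruskal-Wallis test, and "the mean pain scores will be analyzed for significant differences in the area under the curve (AUC) for VAS" by a two-sample t-test. Rescue is not mentioned.

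**Other places that might have dealt with it.** The secondary outcome is operative time and the tertiary outcome is cost-effectiveness based on materials used. Trial discontinuation covers analgesics outside those the trial prescribes, not the trial's own rescue. Missing data covers losses and crossovers.

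**The concern.** The same measurement is both outcome and trigger. A score above 4 at 2 h leads to treatment that can lower the 4 h and 6 h scores, and a score above 4 at 4 h can lower the 6 h score. If one technique leaves patients in more pain, more of them cross the threshold and more of their later scores are reduced. Part of the difference between techniques then moves out of the VAS and into analgesic consumption, which no listed outcome measures.

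In a superiority trial this would cost power. Here the design is equivalence and the stated hypothesis is no significant difference, so a pull towards zero favours the conclusion the trial hopes to reach. Having both an intention-to-treat and a per-protocol analysis does not protect against it: rescue follows the protocol, so rescued scores enter both sets.

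**Working it through.** The plan gives no figure for this effect, so there is none to reproduce. The check asks which scores can be affected, how much they weigh in the AUC, and how large the shrinkage could be.

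**1. Which scores are exposed**
- 2 h: taken before any VAS-triggered rescue, so unaffected.
- 4 h: exposed to rescue triggered at 2 h.
- 6 h: exposed to rescue triggered at 2 h or 4 h.
- Day 7: taken after a 5-day course started on the day of surgery should have ended, so it may be little affected.

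**2. Weight of each score in the AUC**

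The article does not state the AUC rule; the trapezoid rule is assumed. With times 2, 4, 6 and 168 h the span is 166 h.
- 2 h: (2/2)/166 = 1/166 = 0.6%
- 4 h: (2/2 + 2/2)/166 = 2/166 = 1.2%
- 6 h: (2/2 + 162/2)/166 = 82/166 = 49.4%
- Day 7: (162/2)/166 = 81/166 = 48.8%

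The unaffected 2 h score has almost no weight, and the exposed 6 h score carries about half.

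**3. Size of the shrinkage**

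From the protocol: trigger above 4 and SD 1.9 (Sample size determination). Assumed: true means 5 v 4 at every time, within-patient correlation 0.5, scores clipped to 0–10, rescue lowering later scores on the day of surgery by R = 1, 2 or 3 points, and day 7 unaffected.

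Approximation for one time point:

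observed difference ≈ true difference − R × (difference between arms in the proportion already rescued)

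At 4 h the proportion already rescued is the proportion above 4 at 2 h. This is Φ((5 − 4)/1.9) = Φ(0.526) = 0.70 in the arm with more pain and Φ(0) = 0.50 in the other. The true difference after clipping is 0.99. The approximation gives 0.99 − 0.20R = 0.79, 0.59 and 0.39.

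Simulation with 1,000,000 patients per arm agrees:

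| R | 2 h | 4 h | 6 h | Day 7 |
|---|---|---|---|---|
| none | 0.99 | 0.99 | 0.99 | 0.99 |
| 1 | 0.99 | 0.79 | 0.81 | 0.99 |
| 2 | 0.99 | 0.58 | 0.62 | 0.99 |
| 3 | 0.99 | 0.37 | 0.41 | 0.99 |

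By 6 h, 90% v 75% have been rescued. Applying the weights from step 2 gives the time-averaged AUC difference:
- R = 1: (1×0.99 + 2×0.79 + 82×0.81 + 81×0.99)/166 = 149.18/166 = 0.90
- R = 2: (1×0.99 + 2×0.58 + 82×0.62 + 81×0.99)/166 = 133.18/166 = 0.80
- R = 3: (1×0.99 + 2×0.37 + 82×0.41 + 81×0.99)/166 = 115.54/166 = 0.70

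**4. Sensitivity to the assumptions** (correlation 0.6, 200,000 per arm)
- True difference 0.73, lower-arm mean 4, SD 1.9: the AUC difference falls from 0.72 to 0.65, 0.58 and 0.50. If the rescue effect still held at day 7 it would fall to 0.59, 0.45 and 0.30.
- SDs of 2.356 (local) and 1.479 (comparator), as in the sample-size section, with saddle block worse and low pain (means 2 v 2.73): 36% are rescued by 6 h in each arm, and the AUC difference only moves from 0.49 to 0.48, 0.47 and 0.46.

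No scenario gave an observed 4 h, 6 h or AUC difference larger than the rescue-free one. The amount of shrinkage follows the gap in rescue rates, as the formula in step 3 implies.

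**The case against.** **Observed scores under a common rescue rule are a legitimate target.** The rule is the same in both arms, so comparing scores as observed answers a fair question: what pain do patients feel under each technique with the same analgesic policy? This stands. But similar VAS with more analgesia in one arm is not similar pain control, so even this reading needs rescue use shown by arm.

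**An unseen analysis plan may deal with it.** Handling of post-rescue scores is often left to a SAP, and the article does not state that they are treated as if no rescue had been given. That is inferred from the stated tests. What the article does fix is its list of outcomes, which omits rescue use, and its comparisons, which use scores as observed.

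**Stronger readings that a reader might infer, and that the documents do not support:**
- *Day-7 scores are lowered too.* The rescue course lasts 5 days, so nothing in the article establishes this.
- *A true difference of 1 shrinks to the plan's own 0.73.* That figure is the unweighted 2–6 h mean for R = 2, (0.99 + 0.58 + 0.62)/3 = 0.73, a summary the plan does not use. On the AUC the same case gives 0.80.
- *Differences always shrink.* Shrinkage needs unequal rescue rates.
- *An equivalence confidence interval will be passed wrongly.* The analysis section contains only difference tests at p < 0.05.

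**Rescue is not the main threat to the conclusion.** This also stands. At 29 per arm the 95% half-width for a single score is 1.96 × 1.9 × √(2/29) = 0.98, already wider than 0.73. In the first scenario of step 4, the power of the AUC t-test to detect 0.73 is about 37% without a rescue effect, and 35%, 32% and 28% with R = 1, 2 and 3. Rescue adds to that weakness modestly.

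**Conclusion.** The concern holds in limited form. The trigger and the primary outcome are the same scores, the planned comparisons take them as observed, and no primary, secondary or tertiary outcome captures rescue. If rescue rates differ between arms, the 4 h and 6 h differences are attenuated, and so is the AUC through the 6 h score. The direction favours a finding of no difference.

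Under the illustrative assumptions, the 4 h and 6 h differences lose roughly 0.2, 0.4 or 0.6 of a point for rescue effects of 1, 2 or 3 points. The AUC difference loses about 0.1, 0.2 or 0.3. The rescue effect, pain level and correlation are not in the documents, and the AUC rule is assumed. The 2 h score is untouched. The point deserves correction because it limits what a null result can mean, but it does not by itself invalidate the trial.

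**What to change.** Leave the rescue rule unchanged and alter only outcomes and analysis.

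1. Add, as a secondary outcome, the proportion rescued and the time to first rescue by arm, with confidence intervals for the comparison. Read it beside the VAS result.
2. Add a pre-specified sensitivity analysis limited to 2–6 h. After a patient's first rescue, replace each later score in that window by the pre-rescue score if that is higher. Do not carry it to day 7: it would impose a score from hours after surgery on 48.8% of the AUC, after the rescue course has ended. In the simulation with means 5 v 4, this replacement brings the 4 h and 6 h differences back to 0.88–1.01, against a true 0.99.
3. State that similar pain control will not be concluded unless the observed-score result, the rescue comparison and the sensitivity analysis all support it.

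**Cost.** Each rescue dose and its time must be on record, and a few analyses are added. The carried-forward score somewhat overstates 4–6 h pain, so it belongs in a sensitivity analysis and not in place of the primary. Because an interim analysis took place on 10 March 2022, the addition should be dated and reported as made after it.
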